### Secondary objective - health-related quality of life and healthcare costs

To measure (changes in) health-related quality of life of the patients the EuroQol 5-dimensions 5-levels (EQ-5D-5L) will be used. The EQ-5D-5L describes health states over five domains (mobility, self-care, usual activities, pain/discomfort and anxiety/depression) and can be completed in less than 5 min. Dutch tariffs will be applied to each of the health states to obtain utilities, which are anchored at 0 (death) and 1 (full health). EQ-5D-5L utilities will be combined over time using the area under the curve (AUC) method to capture the cumulative QALY health gains over the entire six- or twelve-month follow-up period.

The Trimbos Institute and iMTA Cost questionnaire for Psychiatry (TiC-P) will be used for measuring health care usage (and the costs thereof), patients’ and their family’s out-of-pocket costs, and productivity losses owing to absenteeism and presenteeism. In the Netherlands the TiC-P is the most frequently used health care receipt questionnaire for health-economic evaluation. Completion of the TiC-P will take roughly 10 min.

### Exploratory analyses – specific symptoms associated with depression

The State/Trait Anxiety Inventory (STAI) is a self-report measure which has been proven reliable and sensitive in the assessment of both state and trait levels of anxiety. It is a standard international measure in anxiety research and its Dutch translation has been validated. Filling in the STAI takes approximately 5 min. The Snaith-Hamilton Pleasure Scale (SHAPS) measures anhedonia and takes 5 min to complete. To assess rumination and repetitive negative thinking, the Perseverative Thinking Questionnaire (PTQ) will be administered. The Dutch version shows satisfactory psychometric properties and can be completed in about 5 min. The Holland Sleep Disorders Questionnaire (HSDQ) is a self-assessment questionnaire for sleep disorders which can distinguish between the six sleep disorders classified in the International Classification of Sleep Disorders. The HSDQ can be completed in 10 min. The Leiden Index of Depression Sensitivity – Revised (LEIDS-R) measures cognitive reactivity and can be used as a marker of vulnerability to depression. It takes about 10 min to complete.

### Exploratory analyses – expectancy

The Credibility/Expectancy Questionnaire (CEQ) aims to assess the expectations patients have of a treatment. We have tailored this questionnaire to our study design. The questionnaire consists of eight questions, four of which concern the rTMS treatment, and four of which are about the medication treatment. Questions will be answered with a visual analog scale. Baseline expectations regarding antidepressant treatment have been shown to correlate with treatment outcome [42].

#### Analysis

The clinical outcome data will be analyzed and reported according to the CONSORT guidelines, i.e. primarily on intention-to-treat (ITT) basis.

### Description of the sample

Participant characteristics will be reported in Table 1 of the research paper, showing mean and standard deviation or percentage for each variable.

### Change in depression severity

Our primary outcome during the intervention is overall change in HDRS-17 depressive symptom severity during 8 weeks of treatment by condition (rTMS versus medication). Data will be collected at 6 timepoints: at baseline, and after 5, 10, 15, 20, and 25 rTMS treatment sessions (or corresponding days for participants in the medication arm). We will employ linear mixed modelling using marginal means, with HDRS-17 score as our dependent variable and treatment (rTMS or medication) as independent variable. Age and gender will be added as covariates, since these have been shown to affect the phenomenology of depression.

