## Methods

### Study design

In this pragmatic randomized controlled trial (RCT), patients are randomly assigned to one of two treatment conditions. In the first condition, treatment consists of rTMS combined with CBT and continued antidepressant medication, which will hereafter be referred to as the rTMS arm. In the second condition, treatment consists of a switch from the current antidepressant medication to a tricyclic antidepressant (TCA) or augmentation with lithium or a second-generation antipsychotic, also in combination with CBT. This will be referred to as the medication arm. The trial consists of 8 weeks of unblinded treatment followed by a follow-up of the cohort at four and 6 months from baseline onward. For a subgroup of the patients, an extended follow-up will take place at nine and 12 months from baseline onward to assess effect decay or preservation. See Fig. 1 for the CONSORT flowchart. Patients in the medication arm who did not recover to the medication intervention can receive rTMS after completion of the first 8 weeks of treatment.

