### Sample size calculation

The sample size calculation is based on the outcome of the rTMS arm in comparison to the medication arm. To flag up a clinically significant difference between rTMS and medication, we took an effect size of d = 0.33, which corresponds to the lower boundary of a medium clinically meaningful effect [31] and is similar to effect sizes for research on antidepressant medication [32]. Alpha will be set at 0.05, with a power (1-beta) of 0.80. We will employ a two-sided repeated measures ANCOVA, with a total of six repeated measurements (baseline and measurements corresponding to rTMS treatment 5, 10, 15, 20, and 25). See also Table 1 for an overview and timepoints of the measurements. Based on HDRS-17 data from one of our previous studies, we expect the correlation between baseline and follow-up to be *r* = 0.59, and the correlation between follow-up measurements to be *r* = 0.69. The sample size calculation was performed in STATA version 15.1 and resulted in an estimated required sample size of 59 participants per condition. Compensating for possibly 10% loss to follow-up, the total sample size at baseline will be increased to 132 participants.

**Table 1 Tab1:** Overview of rTMS sessions and measurements during the treatment period. For participants in the medication arm, measurements will be done on days corresponding to treatment day 5, 10, 15, 20, and 25 of rTMS treatment

	Week 1					Week 2					Week 3					Week 4				
Day	1	2	3	4	5	1	2	3	4	5	1	2	3	4	5	1	2	3	4	5
rTMS	x	x		x	x	x	x		x	x	x	x		x	x	x		x		x
HDRS						x						x								x
BDI-II						x						x								x
	Week 5					Week 6					Week 7					Week 8				
Day	1	2	3	4	5	1	2	3	4	5	1	2	3	4	5	1	2	3	4	5
rTMS	x		x		x	x		x		x		x		x			x		x	
HDRS								x											x	
BDI-II								x											x	

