### Interventions

#### rTMS

rTMS treatment will be performed using a Magstim Rapid 2 (Radboudumc) or a Deymed DuoMag XT-35 or XT-100 equipment (neurocare and ETZ) using generic figure-8 coils). All rTMS parameters used in the proposed study are within the range considered safe according to the latest published safety guidelines [34, 35]. Firstly, the resting motor threshold (rMT) will be defined in each participant as the minimal stimulation intensity evoking an MEP of ≥0.05 mV in 50% of the trials in the muscle of the right thumb (M. abductor pollicis brevis). Note that rMT will be determined at the beginning of every week before the first treatment session. We will use BeamF3 (freely available software at (http://clinicalresearcher.org/F3/calculate.php) to find the DLPFC, which is based on electrode position F3 from the EEG 10–20 system [36]. A detailed description of this method can be found in Beam et al., (2009) [36]. The coil will be positioned over this location at an angle of 45° relative to the midline.

rTMS will be conducted using a high-frequent protocol, applying 60 trains of 10 Hz pulses with a duration of 5 s and an inter-train interval of 25 s over the left DLPFC (50 pulses per train, 3000 pulses per session), with an intensity of 120% of the rMT. Twenty-five rTMS sessions will be given over the course of 8 weeks, following a schema of 4, 4, 4, 3, 3, 3, 2, 2 sessions per week. After a minimum of fifteen sessions (corresponding to 4 weeks), treatment may be ended. This is only possible when the scores on the HDRS-17 decrease to a minimum of symptoms (score < 8, in remission) for at least two measurements in a row. However, when the scores still show a decline, the patient is still improving and will likely progress even further. The rTMS sessions should be continued until the patient’s HDRS scores remain below 8 for two measurements in a row but no longer than 8 weeks (given the set-up of the approved ZonMW grant). Table 1 shows an overview of the rTMS treatments and measurements during the eight-week treatment period. Patients responding to rTMS are allowed to receive booster sessions in case of relapse.

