### Primary objective - depressive symptoms

Section A, B and D of the Structured Clinical Interview for DSM 5 disorders (SCID-I; 2018) will be used at baseline and after six and 12 months to assess depressive episodes and possible relapses/recurrences at follow up and extended follow-up. During intake, the SCID will also be used to assess presence of bipolar disorder or psychotic features. The SCID takes about 20 min to complete.

The Hamilton Depression Rating Scale 17 item version is an observer rated scale used to assess the severity of depressive symptoms (HDRS-17) [38]. The HDRS-17 is assessed during screening, treatment, follow-up and extended follow-up. Completion takes approximately 15 min. During the eight-week treatment period, the HDRS-17 will be administered every five rTMS treatments, and on corresponding days for participants in the medication arm. See Fig. 2 for the schedule during treatment. Response is defined as a ≥ 50% reduction in score on the HDRS-17, whereas remission is defined as a score of < 8. Response and remission will be determined after 8 weeks of treatment and at the final follow-up assessment of the RCT at 6 months after baseline.

The Beck Depression Inventory will be used in order to measure individual differences in depressive symptoms (BDI-II) [39]. Participants will be asked to fill in the BDI-II once every five rTMS sessions or on corresponding days when they are in the medication arm. See Fig. 2 for the schedule during treatment. Participants have to indicate on 21 items in how far these items describe themselves on a scale ranging from 0 to 3 resulting in a sum score between 0 and 63. The total score can further be divided into four ranges, describing the severity of depressive symptoms from minimal (0–13), mild (14-19), moderate (20-28) to serious depressive symptoms (29–63). Completion takes about 5 min.

Two questionnaires will be used to assess and quantify the level of treatment resistance. The Dutch Measure for quantification of Treatment Resistance in Depression (DM-TRD) quantifies treatment-resistant depression by assessing treatments in the depressive episode as well as functional impairment, comorbid anxiety, personality disorders and psychosocial stressors [40]. The DM-TRD generally takes 10-20 min to complete after the diagnostic interview. The Antidepressant Treatment History Form (ATHF) can be administered in 10 min or less, depending on the number of antidepressant trials of a patient [41].

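### HDRS-17 visits are tied to delivered sessions in the rTMS arm, so patients who end rTMS early in remission have no defined session-20 and/or session-25 assessment

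*Protocol article*

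**What the plan says.** Two sections of the protocol article tie assessment in the rTMS arm to sessions. Change in depression severity collects HDRS-17 "at baseline, and after 5, 10, 15, 20, and 25 rTMS treatment sessions (or corresponding days for participants in the medication arm". Primary objective - depressive symptoms repeats the trigger: "the HDRS-17 will be administered every five rTMS treatments, and on corresponding days for participants in the medication arm". The Table 1 caption puts the other arm on matched days: "For participants in the medication arm, measurements will be done on days corresponding to treatment day 5, 10, 15, 20, and 25 of rTMS treatment".

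The rTMS section plans 25 sessions in 8 weeks, "following a schema of 4, 4, 4, 3, 3, 3, 2, 2 sessions per week". It then adds: "After a minimum of fifteen sessions (corresponding to 4 weeks), treatment may be ended". The condition is that HDRS-17 scores "decrease to a minimum of symptoms (score < 8, in remission) for at least two measurements in a row". The same section favours continuing while scores are still falling, so ending early is optional.

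The outcomes need data to week 8. The primary outcome is change over 8 weeks with six timepoints, the Analysis section commits to intention to treat, and for the binary outcomes: "Response and remission will be determined after 8 weeks of treatment and at the final follow-up assessment of the RCT at 6 months after baseline". Evaluation of treatment response and remission asks for the percentage per arm at each time point.

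**The concern.** A session-defined visit exists only if the session is delivered. A patient below 8 at sessions 10 and 15 may stop before session 20; one below 8 at sessions 15 and 20 may stop before session 25. For these patients the text gives no trigger for the remaining assessments. A medication patient with the same course is still rated on the matched days.

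At stake is loss of outcome data that depends on the outcome, in one arm only, among the patients who did best. It bears most on the week-8 response and remission percentages and less on the primary model. The later visits are not affected: they are timed from baseline in both arms ("followed by a follow-up of the cohort at four and 6 months from baseline onward").

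**Working it through.** **1. The plan's own figures.** Inputs from Sample size calculation: d = 0.33, two-sided alpha 0.05, power 0.80, correlation 0.59 between baseline and follow-up, 0.69 among follow-ups, p = 5 follow-ups.
- Variance factor for repeated-measures ANCOVA: v(p) = (1 + (p − 1) × 0.69)/p − 0.59². For p = 5: 3.76/5 − 0.3481 = 0.4039.
- n per arm = 2 × 0.4039 × (1.960 + 0.842)²/0.33² = 58.2, so 59. Total 118/0.90 = 131.1, so 132.

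Both stated figures reproduce. The sample size is not in question.

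**2. What an early end removes.** Table 1 has 4+4+4+3+3+3+2+2 = 25 sessions. Counting its marks:

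| Session | Week, day | Calendar day |
|---|---|---|
| 5 | 2, 1 | 8 |
| 10 | 3, 2 | 16 |
| 15 | 4, 5 | 26 |
| 20 | 6, 3 | 38 |
| 25 | 8, 4 | 53 |

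These are the days carrying HDRS and BDI-II marks. Ending at session 15 removes days 38 and 53 (2 of 5 follow-ups). Ending at session 20 removes day 53 (1 of 5).

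**3. Power.** v(4) = 0.4194 and v(3) = 0.4452. With 59 per arm, power is 80.5% with all five follow-ups. If 10%, 30% or 50% of the rTMS arm ended at session 15, approximate power would be 80.3%, 79.9% or 79.5%. The loss is about one percentage point or less.

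**4. Observed week-8 remission.** Let p be true remission, s the share ending early, and m remission among them. If early enders leave the denominator, observed remission = (p − s·m)/(1 − s). Take p = 0.56, the remission rate the Background cites from a naturalistic cohort:
- s = 0.073, m = 0.98: (0.56 − 0.0715)/0.927 = 52.7%.
- s = 0.27, m = 0.914: (0.56 − 0.2468)/0.73 = 42.9%.

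The shares s and m come from simulation with the document's correlations. Baseline mean 22, SD and trajectory are assumptions. Everyone who met the rule stopped, and nobody who stopped was assessed again.

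| Scenario (SD 5–7) | End early | Observed week-8 remission | Raw week-8 mean too high by |
|---|---|---|---|
| True remission 56% | 6–33% | 40–53% | 0.5–2.7 points |
| True remission 35% | 3–18% | 25–33% | 0.3–1.6 points |
| rTMS mean 10–14 at session 25 | about 2–14% | not tabulated | 0.2–1.3 points |

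In the first two scenarios, 82–99% of those missing would have been remitters. For scale, d = 0.33 at an assumed SD of 6 is 0.33 × 6 = 2.0 points.

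**5. The planned estimator.** The last column is a raw mean of observed values, not the planned analysis. Simulating the same rule at 56% remission with SD 6–7, the raw week-8 mean was off by 0.8–3.0 points. A likelihood estimate using the earlier visits was off by less than 0.02. This holds because the simulated stopping depends only on recorded scores, and because later scores were generated as if treatment had continued.

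**The case against.** The strongest reply is that the article ends treatment early, not assessment. Six timepoints over 8 weeks without exception, intention to treat, and week-8 remission in each arm all suggest that a week-8 rating is meant for everyone. Fig. 2, to which the article refers for the assessment schedule, is not shown. That may well be the intent. But the two sections that define the visits give only the session trigger, and followed as written it cannot deliver those outcomes. A reader might infer that the plan states early enders are not assessed; it does not. The defect is that its rules do not fit together.

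A reader might also infer that the primary treatment effect is biased by the raw differences above. It is not shown to be. Stopping driven by recorded HDRS-17 scores is missing at random, and a correctly specified mixed model largely absorbs it. Two qualifications remain. Ending is discretionary, so recorded scores may not fix it fully. And the model would project early enders as if rTMS had continued, which is not their actual course under intention to treat; nothing here quantifies that difference.

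The percentages fall only if early enders leave the denominator, and the article speaks of participants under intention to treat. In the planned Cox analysis they may already count as remission events. Both points stand and narrow the exposure.

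Finally, missed or postponed sessions could move rTMS visits later than the matched medication days. The article gives no information on how often, so neither a size nor a net direction can be claimed.

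**Conclusion.** The point holds as a conflict between stated rules, worth a cheap correction. Taken literally, the session-based visits and the early-end rule leave some rTMS patients without a session-20 and/or session-25 HDRS-17, while every medication patient keeps a defined day. The conflict and its one-arm nature follow from the text alone.

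The main exposure is the observed week-8 response and remission percentages, biased against rTMS if early enders are left out. The simulated falls in remission are upper-end illustrations: SD, baseline mean and trajectory are assumed, the 56% comes from a cohort whose CBT format the article says differs, and every qualifier was made to stop. The primary mixed model is largely protected apart from what it estimates for early enders. The sample size stands.

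**What to change.** Leave the treatment-ending rule unchanged and change only the assessment definition, for example: *HDRS-17 and BDI-II are assessed in both arms on fixed calendar days from the start of allocated treatment (week 2 day 1, week 3 day 2, week 4 day 5, week 6 day 3, week 8 day 4), with the same window, irrespective of the number of sessions received or an early end of rTMS.* Index the mixed model by these visits, and define week-8 response and remission on the week-8 visit for everyone randomised.

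The days are those already in Table 1, so no timepoint is added. The cost is a wording change, a common visit window, and at most two HDRS/BDI-II contacts for each patient who ends rTMS early, both already in the schedule.

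### The sample size rests on adjustment for baseline HDRS-17, but the primary model as stated leaves baseline out of its covariates; without it, power falls short of 80%

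*Protocol article*

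**What the plan says.** The section Sample size calculation states the method: "We will employ a two-sided repeated measures ANCOVA, with a total of six repeated measurements". The six are baseline plus five measurements tied to rTMS sessions 5, 10, 15, 20 and 25. The inputs are an effect size ("we took an effect size of d = 0.33"), the error rates ("Alpha will be set at 0.05, with a power (1-beta) of 0.80"), a baseline correlation ("we expect the correlation between baseline and follow-up to be *r* = 0.59") and a correlation of 0.69 among the follow-up scores. The result is 59 per condition, raised to 132 in total for 10% loss.

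The section Change in depression severity describes the primary outcome as overall change in HDRS-17 during the 8 weeks, by condition. It lists the same six collection times and gives the model as "linear mixed modelling using marginal means, with HDRS-17 score as our dependent variable and treatment (rTMS or medication) as independent variable". It then says "Age and gender will be added as covariates", with a reason for choosing those two. Baseline HDRS-17 is not among the covariates, and no time or treatment-by-time term is named.

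**The concern.** The two sections give two different accounts of the primary analysis of the same outcome. The first needs baseline HDRS-17 as a covariate, because the 0.59 correlation reduces the required sample only if baseline is adjusted for. The second lists its covariates and baseline is not one of them.

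If the analysis follows the second section, the variance reduction that justifies 59 per arm is lost, and the trial could well miss the effect it was designed to detect. The contrast is also unsettled. A treatment effect on the score, a change from baseline and a treatment-by-time test are different quantities with different power, and the section's wording allows more than one of them.

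The protocol itself treats baseline severity as prognostic: the Randomization section stratifies on HDRS-17 of 17–23 versus above 23.

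**Working it through.** **Inputs from Sample size calculation:** d = 0.33; two-sided alpha 0.05; power 0.80; r0 = 0.59 (baseline with follow-up); r = 0.69 (between follow-ups); one baseline and five follow-ups; 59 per arm.

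**Assumptions not in the document:** d = 0.33 at every post-baseline visit; equal variance at each visit; 1:1 allocation.

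**Step 1. Reproduce the plan's figure.** In SD² units, the variance factor of the mean of five follow-ups adjusted for baseline is

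(1 + 4 × 0.69)/5 − 0.59² = 0.752 − 0.3481 = 0.4039.

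n per arm = 2 × (1.960 + 0.842)² × 0.4039 / 0.33² = 58.2, so 59. Adding 10% loss: 118/0.9 = 131.1, so 132. Both stated figures match. Power at 59 is Φ(0.33/√(2 × 0.4039/59) − 1.96) = Φ(2.82 − 1.96) = 80.5%.

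**Step 2. Apply the same power formula to other readings of the analysis section,** where z = effect/√(2 × factor/59).

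- Mean of the five post-baseline scores, no baseline: factor 0.752.
- Average change from baseline: factor 0.752 + 1 − 2 × 0.59 = 0.572.
- 5-df treatment-by-time test: noncentrality 0.33²/(2 × 0.572/59) = 5.62.
- Treatment main effect over all six scores, equal weights: effect 0.33 × 5/6 = 0.275; factor (6 + 10 × 0.59 + 20 × 0.69)/36 = 25.7/36 = 0.714.
- The same main effect with generalised least squares weights: baseline weight 0.283; effect 0.33 × (1 − 0.283) = 0.237; factor 0.706.

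| Reading | Effect (SD) | Factor | z | Power, 59 per arm | Power, 66 per arm | n per arm for 80% |
|---|---|---|---|---|---|---|
| Baseline-adjusted, or baseline means constrained equal | 0.33 | 0.404 | 2.82 | 80.5% | 84.7% | 59 |
| Average change from baseline | 0.33 | 0.572 | 2.37 | 65.9% | 70.8% | 83 |
| Mean of five, unadjusted | 0.33 | 0.752 | 2.07 | 54.3% | 58.9% | 109 |
| Main effect over six, equal weights | 0.275 | 0.714 | 1.77 | 42.4% | 46.4% | 149 |
| 5-df treatment-by-time | – | – | – | 40.6% | 45.2% | – |
| Main effect over six, GLS weights | 0.237 | 0.706 | 1.53 | 33.3% | 36.6% | – |

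**Step 3. Give credit for age and gender.** The document states no explained variance. If they explained an assumed 0–20%, power at 59 per arm would be 54–64% for the unadjusted mean of five and 42–51% for the equal-weight main effect. For the change and treatment-by-time readings, covariates entered only as main effects drop out of a within-patient change and add nothing.

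**Step 4. Dependence on the assumed effect.** For the two averaged contrasts without dilution, the sample needed relative to the plan depends only on the variance factors: 0.752/0.4039 = 1.86 for the unadjusted mean and 0.572/0.4039 = 1.42 for average change. These ratios hold whatever the size of d.

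**The case against.** The strongest reply is that the analysis section is loosely worded rather than wrong. Its mention of six timepoints is a statement about data collection and does not say that baseline is an outcome row. The sample size section lists the same six and there means one baseline plus five follow-ups. The outcome is described as a change, which a main effect on the score does not estimate. A mixed model with baseline means constrained equal keeps the full 80.5%, so the class of model is not at fault. Time coding, covariance structure and the exact contrast are details that a journal article may leave to a fuller document.

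Most of this stands, and it rules out several stronger claims that a reader might infer:

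- That the primary analysis has 42% power. That figure needs baseline as an outcome row, a treatment main effect and equal weights, and the text fixes none of these.
- That the reported difference will be diluted by 17% or more. This follows only if baseline is kept as an outcome under a main effect.
- That the sample size is wrong. It is right for its own method.
- That the unnamed time terms are a defect in themselves.

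What the reply does not remove is the conflict over baseline. The section is not silent on covariates: it names two and omits the one on which the sizing depends. An analysis plan that followed the list as written would carry the conflict forward. Counting all 66 per arm as complete does not answer the point either, since the highest unadjusted figure in the table is then 70.8%.

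**Conclusion.** The inconsistency is real. Of the readings examined, the stated 80% power holds only when baseline HDRS-17 is adjusted for or the baseline means are constrained equal. Readings without that give about 33–66% at 59 per arm: 66% for average change, 54% for the unadjusted post-baseline mean, 41% for the 5-df test, and 33–42% with baseline kept as an outcome. Only in that last case is the estimate also diluted, to 0.24–0.275 SD instead of 0.33.

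The figures rest on the protocol's own correlations and on a constant d = 0.33 from the first post-baseline visit, which the document does not state. The document does not show which analysis will be run, so the conclusion is that the two sections disagree and that the power claim depends on how this is resolved. It does not follow that the trial is underpowered by a known amount.

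**What to change.** Bring Change in depression severity into line with Sample size calculation:

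- Take the five post-baseline HDRS-17 scores as outcome and add baseline HDRS-17 as a covariate alongside age and gender. Alternatively, use a longitudinal model with the baseline means constrained equal between arms.
- Include visit and treatment-by-visit terms.
- Name the average of the five post-baseline treatment differences as the primary 1-df test, and say that the 80% power refers to that contrast.

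The stated 59 per arm and 132 in total then stand. Baseline HDRS-17 is already collected, so the cost is a rewording of one section, or a statement in the analysis plan, made before outcome data by arm are seen.

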### Randomization

Participants will be randomly assigned to either the rTMS or medication arm. Randomization will be done via Castor EDC and will be stratified for treatment center, total number of depressive episodes, and current depression severity (moderate: HDRS-17 score of 17–23; severe: HDRS-17 score of > 23). Castor EDC randomizes participants with a four and six block design. More information about the randomization algorithm can be found on Castor’s website (https://helpdesk.castoredc.com/article/50-the-randomizationalgorithm-in-castor).

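### The primary model names age and gender but none of the three stratification factors: conservative to the extent these are prognostic, and baseline HDRS-17 is needed for the planned 80% power

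*Protocol article*

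**What the plan says.** Under Randomization, the protocol article states that allocation is "stratified for treatment center, total number of depressive episodes, and current depression severity", with severity split at an HDRS-17 of 17–23 against above 23. On blocking it says: "Castor EDC randomizes participants with a four and six block design".

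Under Change in depression severity, the primary analysis is a linear mixed model "with HDRS-17 score as our dependent variable and treatment (rTMS or medication) as independent variable". Covariates get one sentence: "Age and gender will be added as covariates, since these have been shown to affect the phenomenology of depression". No stratification factor is named there. Baseline HDRS-17 appears only as the first of the repeated outcome measurements: "Data will be collected at 6 timepoints: at baseline, and after 5, 10, 15, 20, and 25 rTMS treatment sessions".

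Under Sample size calculation, the method is different: "We will employ a two-sided repeated measures ANCOVA, with a total of six repeated measurements". The planning values are "we took an effect size of d = 0.33" and "Alpha will be set at 0.05, with a power (1-beta) of 0.80", a baseline-to-follow-up correlation of 0.59 and a correlation of 0.69 among follow-up measurements. They lead to 59 per arm, and to 132 in total after allowing for 10% loss.

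**The concern.** Stratified blocks force the arms to be similar on the stratification factors, so between-stratum variation largely drops out of the treatment contrast. If the model leaves the factors out, that variation stays in the residual. The reported standard error then exceeds the true sampling variability, confidence intervals are too wide, and the type I error falls below its nominal 5%. The point estimate is unaffected.

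The article does more than stay silent. It chooses covariates and gives a reason for them, and the choice passes over the variables that the design balances. One of these, severity, is a coarse form of baseline HDRS-17, on which the sample size depends.

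**Working it through.** **Inputs from the article:** d = 0.33, two-sided alpha 0.05, power 0.80, one baseline and five follow-up measurements, correlations 0.59 and 0.69, 59 per arm, 10% loss.

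**1. Reproducing the planned size.** With baseline as a covariate, the variance factor for the mean of five follow-ups is (1 + 4 × 0.69)/5 − 0.59² = 0.752 − 0.3481 = 0.4039.
- n per arm = 2 × (1.96 + 0.8416)² × 0.4039/0.33² = 58.2, so 59.
- 59/0.9 = 65.6, so 66 per arm and 132 in total.
- SE = √(2 × 0.4039/59) = 0.1170, 0.33/0.1170 = 2.820, and power = Φ(2.820 − 1.96) = 0.805.

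The stated figures reproduce exactly.

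**2. The same 59 per arm without baseline adjustment.**

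| Analysis | Variance factor | Power at 59 per arm | n per arm for 80% |
|---|---|---|---|
| Follow-up mean, baseline ignored | 0.752 | 0.543 | 109 |
| Change from baseline | 0.752 + 1 − 2 × 0.59 = 0.572 | 0.659 | 83 |
| Baseline as covariate | 0.4039 | 0.805 | 59 |

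Only the last row supports the stated size.

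**3. Centre and episodes, once baseline is in the model.** The article gives no figure for how prognostic these two are. Let R² be the share they explain of the variance left after baseline adjustment (an assumption), and assume good balance within strata. Then the true SD of the estimate is 0.1170 × √(1 − R²) whether or not the factors are modelled. The model SE shrinks to match only if they are.
- Omitted: power = Φ((2.820 − 1.96)/√(1 − R²)); type I error = 2 × (1 − Φ(1.96/√(1 − R²))).
- Included: power = Φ(2.820/√(1 − R²) − 1.96); type I error 5%.

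| Assumed R² | Power, omitted | Power, included | Gain (points) | Type I error, omitted |
|---|---|---|---|---|
| 0 | 80.5% | 80.5% | 0 | 5.0% |
| 5% | 81.1% | 82.5% | 1.3 | 4.4% |
| 10% | 81.8% | 84.4% | 2.7 | 3.9% |
| 20% | 83.2% | 88.4% | 5.2 | 2.8% |

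**4. Simulation with imperfect balance.** Stratified blocks of 4 and 6 were simulated with N = 118 and 3,000 runs per scenario, analysed by subject-level regression on complete data. Assumed: six centres, two episode classes, severity cut at the median, age and gender not prognostic, and centre plus episodes explaining 0, 8 or 15% of the residual variance. Under baseline-adjusted analysis the model SE was 0 to 6% too large with the factors omitted. Power was 0.79–0.80 with them omitted and 0.79–0.83 with them included. Monte Carlo error on each power figure is about √(0.8 × 0.2/3000) = 0.7 points, so the small differences are only indicative.

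**The case against.** **The text is condensed.** The primary-analysis paragraph also leaves out time, interaction and random effects, and it does not say that age and gender are the only covariates. A full analysis plan may list more. That is fair, but the article does name and justify its covariates, so the choice can be commented on.

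**Severity may already be covered.** If the mixed model conditions on baseline, as the sample size section implies, severity is largely absorbed and only centre and episodes remain. This stands. For that reason step 3 starts from the baseline-adjusted 80.5% and credits nothing further to severity. It is also wrong to compare 80.5% with 82.5/84.4/88.4% and claim 2, 4 or 8 points. Stratification already brings part of the gain when the factors are omitted, so the correct comparators are 81.1/81.8/83.2%.

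**Balance will be imperfect and centre terms cost degrees of freedom.** The Procedure section lists six organisations, or 11 sites if locations count separately. With two severity classes and at least two episode classes (assumed), that makes 24 to 44 strata for 132 patients, or 5.5 to 3 patients each, against blocks of 4 and 6. A second simulation (N = 118, 5,000 runs, baseline adjusted) at R² of 5/10/20% gave power changes of 80.1→81.4, 80.5→82.8 and 82.4→88.1 with six centres. With 11 sites it gave 80.5→79.7, 80.0→81.7 and 81.8→86.2. Fitting many small sites can therefore cancel a small gain. This stands and bears on how centre is entered.

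**Stronger readings that the article does not support.** A reader might infer that omitting the strata leaves the trial underpowered. The planned 80% never relied on adjusting for centre or episodes. The large losses in step 2 come from how baseline is handled. A reader might also carry the criticism to the Cox models for response and remission, but the article lists no covariates for those, and an article may leave that to the analysis plan. Nor does the article report rater differences by centre. The rTMS device does vary by site, but it affects one arm only.

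**Conclusion.** The point holds at moderate size. The design stratifies on three factors and the stated primary model adjusts for none of them. The consequence is conservative: a standard error that is too large to the extent the factors are prognostic, with no bias in the estimate.

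Two parts differ in certainty. For severity, the article's own r = 0.59 shows that it is prognostic, and the planned 59 per arm needs baseline HDRS-17 as a covariate, or an equivalent use of it, for 80% power. For centre and episodes, the size rests on an assumption: about 1 to 3 points of power if they explain 5 to 10% of the remaining variance, about 5 at 20%, and none if they are not prognostic or if many small sites use up the gain. These figures are normal approximations that assume good balance within strata.

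**What to change.** In the primary-analysis paragraph, and in the analysis plan, add the following beside age and gender:
- continuous baseline HDRS-17, which covers the severity stratum and brings the model into line with the repeated measures ANCOVA used for the sample size;
- number of depressive episodes, in the categories used for randomisation;
- treatment centre, as a random intercept, or as a fixed effect with small centres pooled by a rule set before the outcome data are analysed. Treatment is open, so the rule cannot be tied to unblinding.

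Age and gender may stay. The cost is one line in the analysis plan and a few degrees of freedom for centre. The stratification factors are needed at randomisation in Castor EDC, so no new data are required.
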